### Inflammatory Biomarkers and Exercise

Interleukin-10 (IL-10); an anti-inflammatory cytokine is thought to inhibit proteolysis [18] while low levels have been postulated to lead to excessive inflammation and muscle damage [19]. IL-10 is known to attenuate the synthesis of TNF-α surface receptor and its suppressive effects may be beneficial in pathology that results from inflammatory dysregulation such as in sepsis.

A number of studies [20-22] in healthy and other diseased populations; such as in chronic heart failure, have shown that aerobic and resisted exercise alters pro-inflammatory cytokines specifically decreasing IL-6 and TNF-α and increasing IL-10. Simple physical exercises such as repetitive passive muscle stretches have been shown to decrease pro-inflammatory cytokine (IL-6), increase anti-inflammatory cytokine (IL-10) and improve the IL-10/TNF-α ratio in chronic critically ill patients [23]. The use of electrical muscle stimulation on major muscle groups has been shown to attenuate the production of TNF-α [24]. It is therefore important to investigate the effect of exercise on IL-10 in sepsis.

Our pilot study tested 20 patients with sepsis syndromes randomised into a treatment (proactive rehabilitation) and a control group. The trial demonstrated significant decreases (-7.2%) in the percentage fat free mass in the control group with no decreases in the intervention group. Significant increases in IL-10 (mean difference 12.1 [SE +/- 2.1], p < 0.01) were found in the treatment group. Clinically relevant findings from this study indicate early exercise reduces loss of muscle mass in sepsis [25].

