### Hypotheses and Aims

The primary research hypothesis of the "i-PERFORM Trial" is that patients with defined sepsis syndromes [57] in the ICU who participate in an early targeted rehabilitation program will have improved physical function and an improved quality of life. The secondary hypotheses is that there will be systemic effects underlying primary improvements which will include; increased fat free mass; decreased pro-inflammatory and increased anti-inflammatory cytokines; increased peripheral blood mitochondrial DNA content and reduced blood lactate levels; and improved tissue oxygenation and microcirculation flow.

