#### Muscle Mass

Fat free mass will account for muscle mass (lean tissue) measured at baseline (week 0) and weekly thereafter (till ICU discharge) using the Multi-Frequency Bioelectrical Impedance Spectroscopy (BIS) Machine (ImpediMed SFB7, ImpediMed Ltd, Brisbane, Australia). Measurements will be taken at a standardised time of the day as practicable for validity [67] and at standardised anatomical landmarks for reproducibility of results [68]. Pairs of gel electrodes will be placed on the hand and foot on the right side of the body with the participant positioned in supine. ICU monitoring will continue during measurement without interference [69]. An estimate will be made of the critically ill patients' fluid balance. Urinary catheters will be emptied, prior to measurement. If subjects are known to have ascites, a pleural effusion or a renal replacement therapy, measurements will not be done. Percentage fat free mass will be measured in triplicate and analysed to reflect if proteolysis had occurred and resulted in the loss of muscle mass [70].

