### Data Management and Statistical Analysis

A baseline comparison using both student t-tests and chi-square for equal proportions of demographic data will be done between groups at enrolment. Data will be analyzed using SPSS Version 17.0. The distribution, range of scores and heterogeneity will be examined for participants in both groups. Mean changes scores, standard deviations and 95% confidence intervals will be calculated and specific analysis detailed under each outcome measure will be performed. Repeated measures, between/within analysis of variance (ANOVA) will be performed to investigate for the main effects of time and group. Post hoc analyses will then be performed to ascertain where the differences occur. A Bonferroni correction will be used as the post hoc measure as there are multiple outcome measures. Analysis will be by both intention-to-treat and per-protocol method. Any violations of the protocol will be noted. Statistical significance will be set at p < 0.05 and p < 0.025(two-tailed). All efforts will be taken to avoid missing data but if it occurs a carry forward imputation will be done and linear mixed modelling will be used for overall analysis. Reasons for loss of follow up will be recorded.

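### The muscle hypothesis concerns fat free mass, but the variable analysed is percentage fat free mass with no stated denominator; as a share of current weight it understates or cancels lean loss

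*Protocol article*

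**What the plan says.** Three places in the protocol article bear on the muscle outcome.

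- **Hypotheses and Aims** lists "increased fat free mass" first among the systemic effects expected to underlie the primary improvements. This is an amount.
- **Muscle Mass**, opening sentence: "Fat free mass will account for muscle mass (lean tissue) measured at baseline (week 0) and weekly thereafter". Again an amount, used as the stand-in for muscle.
- **Muscle Mass**, closing sentence: "Percentage fat free mass will be measured in triplicate and analysed to reflect if proteolysis had occurred". This is a ratio, and it is the quantity from which loss of muscle is to be inferred.

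The pilot summary under Inflammatory Biomarkers and Exercise has the same pattern. It reports "significant decreases (-7.2%) in the percentage fat free mass in the control group" and concludes that "early exercise reduces loss of muscle mass in sepsis".

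The Muscle Mass section does not say what the percentage is a percentage of. It schedules no weighing and plans no companion analysis of absolute fat free mass or fat mass. Its safeguards concern fluid: an estimate of fluid balance, emptying of urinary catheters, and the rule that "If subjects are known to have ascites, a pleural effusion or a renal replacement therapy, measurements will not be done". None concerns fat or body weight.

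**The concern.** Percentage fat free mass, as normally understood, is fat free mass divided by current body weight. Lean tissue is then in both numerator and denominator, and fat is in the denominator. Such a ratio can stay still while muscle is lost, and can move while muscle is unchanged. This needs no fluid shift; it is a property of the ratio.

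At stake is the inference about proteolysis. If lean and fat waste together, the analysed variable could report no muscle loss where there was a real one. If fat is stable, a true difference between arms in lean loss would appear much smaller in relative terms than it is.

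**Working it through.** The document gives no effect size, standard deviation or sample size for fat free mass, so there is no stated figure to reproduce. The check is algebra with illustrative body composition.

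**Inputs.** From the document: the amount in the hypothesis, the ratio in the analysis, and the pilot's -7.2% (whether points or relative change is not stated). Assumed, because the document gives no body composition data: weight 80 kg; 60%, 70% or 80% fat free at baseline; a lean loss of 7.2% (size borrowed from the pilot figure); and a range of fat losses.

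**Formula, current weight as denominator.** With F = fat free mass, A = fat mass and p = F/(F + A):

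- Percentage = 100 × F/(F + A).
- For small changes, change in points ≈ 100 × p(1 − p) × (dF/F − dA/A).

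The variable therefore responds to proportional lean change minus proportional fat change. With stable fat, the relative change in the percentage is about (1 − p) times the true relative lean change.

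**Lean loss of 7.2%, fat stable (exact).**

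| Baseline % fat free | After | Points | Relative change | Share of true loss shown |
|---|---|---|---|---|
| 60 | 58.19 | -1.81 | -3.01% | 3.01/7.2 = 42% |
| 70 | 68.41 | -1.59 | -2.27% | 2.27/7.2 = 32% |
| 80 | 78.78 | -1.22 | -1.53% | 1.53/7.2 = 21% |

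**Fat also changing (80 kg, 70% fat free: 56 kg lean, 24 kg fat).**

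- Lean -7.2% (4.03 kg), fat -7.2% (1.73 kg): 70.0 to 70.0. The loss is cancelled, and this holds at 60% and 80% too.
- Lean -7.2%, fat -10.8% (2.59 kg): 70.0 to 70.8, a rise of 0.8 points.
- Lean unchanged, fat -2 kg: 56/78 = 71.8%, a rise of 1.8 points (1.5 at 60%, 2.1 at 80%).

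**Fixed baseline weight as denominator.** The same 4.03 kg lean loss gives (56 − 4.03)/80 = 64.96%, that is -5.04 points or -7.2% relative, whatever happens to fat. There is no distortion. The same is true if the percentage meant change relative to baseline fat free mass.

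**What the pilot figure implies (80 kg, 70% fat free, fat stable).** With current weight, -7.2% would need 11.5 kg of lean loss if relative, or 15.5 kg if points. With fixed weight it would need 0.072 × 56 = 4.0 kg, or 0.072 × 80 = 5.8 kg.

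**Fluid.** If 4 kg of retained fluid is counted as fat free mass, the kg value goes from 56 to 60 (+7.1%) and the current-weight percentage from 70.0 to 60/84 = 71.4 (+2.0% relative). A 4 kg muscle loss moves the kg value by -7.1% and the percentage to 52/76 = 68.4 (-2.3% relative). The ratio shrinks artefact and signal by about the same factor.

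**The case against.** The strongest objection is that everything turns on a denominator the article does not state. A fixed baseline weight removes the problem, and the large lean losses that a current-weight reading would require of the pilot figure could be taken as evidence for a fixed weight. An article may also leave such a definition to the full protocol or analysis plan. This stands in part. The distortion is conditional, and an unstated denominator would not by itself be a finding. But the article does state which quantity is hypothesised and which is analysed, and they differ. Nothing in it points to a fixed weight, and current weight is the ordinary meaning of the term.

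A second objection is that kg values are more exposed to fluid, the main measurement worry in sepsis and the one the Muscle Mass section addresses. In absolute terms this is true. It does not favour the percentage, because the current-weight ratio shrinks muscle signal and fluid artefact alike.

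A reader might also infer that the trial would credit exercise with sparing muscle when it had only reduced fat. The document does not support that. It would require fat change to differ by arm, and no figure in the article shows any fat loss, let alone a difference between arms. The fat losses above are chosen for illustration. The arms are designed to differ in activity, so a difference is possible, but that is conjecture. Without it the effect is mainly attenuation, which does not reverse the comparison.

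**Conclusion.** The mismatch is real: fat free mass is hypothesised and taken as muscle mass, while percentage fat free mass is analysed to judge proteolysis, with no denominator given. If the denominator is current weight, the variable shows about 20-40% of the true relative lean loss when fat is stable (assuming 60-80% fat free at baseline), and none of it when lean and fat fall in proportion. If it is a fixed baseline weight, there is no distortion. It would go too far to say that muscle loss will be hidden, or that the comparison between arms is biased: the first depends on the denominator, and the second also on a difference in fat change that the document does not establish. The outcome is secondary and mechanistic; the primary outcomes and the 252 participants are unaffected. The change is nonetheless worth making, because it is right under either denominator: kg is equivalent to the percentage up to scaling if weight is fixed, and free of the fat-change error if it is current.

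**What to change.** In the Muscle Mass section, make fat free mass in kg the analysed variable: change from baseline, adjusted for baseline fat free mass, matching Hypotheses and Aims. Interpret it alongside the fluid-balance estimate already planned. Keep percentage fat free mass, with its denominator stated, as a supporting result so that the pilot comparison is preserved.

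The cost is a wording change and one changed analysis variable. The percentage is formed from fat free mass, so the main analysis needs no new measurement. If the supporting percentage is defined on current weight, a weight is needed at each reading; a current-weight percentage already presupposes one, although the article schedules none. There are two downsides. The kg values move one-for-one with retained fluid, though the percentage offers no better muscle-to-fluid signal. Direct comparability with the pilot moves from the main result to the supporting one.

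### A change in bioimpedance percentage fat free mass is to be read as proteolysis and muscle loss, but the index depends on body water and cannot carry that inference alone in septic patients

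*Protocol article*

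**What the plan says.** The Muscle Mass section (Secondary Outcome Measures) sets the schedule and the interpretation together: "Fat free mass will account for muscle mass (lean tissue) measured at baseline (week 0) and weekly thereafter (till ICU discharge"). The readings are taken "using the Multi-Frequency Bioelectrical Impedance Spectroscopy (BIS) Machine". The inference follows: the percentage is taken three times and "analysed to reflect if proteolysis had occurred and resulted in the loss of muscle mass".

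The section also takes precautions about fluid. "An estimate will be made of the critically ill patients' fluid balance"; catheters are emptied first; the time of day is standardised as far as practicable; and patients known to have ascites, a pleural effusion or renal replacement are not measured.

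Two other places give the outcome its weight. Hypotheses and Aims puts a rise in fat free mass first among the secondary effects. The section Inflammatory Biomarkers and Exercise describes a pilot of 20 randomised patients and reports "significant decreases (-7.2%) in the percentage fat free mass in the control group with no decreases in the intervention group". It then reads this as exercise reducing the loss of muscle.

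**The concern.** Bioimpedance does not observe muscle. It estimates body water and divides by an assumed hydration of lean tissue to obtain fat free mass. This is the general measuring principle and is not stated in the article, but the article's own precautions make sense only if fluid distorts the reading.

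The trial enrols septic patients ventilated for at least 48 hours, and the article's definition of septic shock presupposes fluid resuscitation. The precautions deal with local collections and renal replacement. They do not reach generalised oedema, or resuscitation fluid that is present at one weekly reading and gone at the next.

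What is at stake is the conclusion that the trial may draw. As worded, a fall in the index would be reported as proteolysis, and a smaller fall in the intervention arm as muscle preserved, although water alone could produce either.

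**Working it through.** **Inputs from the article.** The pilot control-arm change is −7.2%. No baseline value, standard deviation or body weight is given, and it is not said whether the figure is relative or in percentage points. The change therefore cannot be reproduced and serves only as a yardstick of size. The article gives no fluid volumes.

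**Assumptions, not in the article.** Weight W = 80 kg (range 60–100), baseline fraction p = 0.70 (range 0.60–0.80), hydration h = 0.732 (range 0.70–0.75), no change in tissue.

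**Formulas.** Fat free mass = body water / h, so losing L litres of water lowers it by L/h kg. With t the fraction after the fall:

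- weight re-measured: (pW − L/h)/(W − L) = t, so L = W(p − t)/(1/h − t)
- weight held fixed: (pW − L/h)/W = t, so L = W(p − t)h

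**7.2% relative fall.** t = 0.70 × 0.928 = 0.6496 and W(p − t) = 4.032.
- re-measured: 4.032/(1.3661 − 0.6496) = 5.6 L
- fixed: 4.032 × 0.732 = 3.0 L

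**Fall of 7.2 percentage points.** t = 0.628 and W(p − t) = 5.76.
- re-measured: 5.76/(1.3661 − 0.628) = 7.8 L
- fixed: 5.76 × 0.732 = 4.2 L

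| Reading of 7.2 | Weight | 80 kg, 70%, h 0.732 | Full assumed range |
|---|---|---|---|
| relative % | re-measured | 5.6 L | 3.0–9.8 L |
| relative % | fixed | 3.0 L | 1.8–4.3 L |
| points | re-measured | 7.8 L | 4.8–11.9 L |
| points | fixed | 4.2 L | 3.0–5.4 L |

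**A different starting point.** Let the same patient begin with excess fluid and return to a true 70%. Clearing 5 L takes the index from (56 + 5/0.732)/85 = 73.9% to 70%, a relative fall of 5.3% with weight re-measured. With weight fixed it goes from 62.8/80 = 78.5% to 70%, a fall of 10.9%. For 3 L and 8 L the falls are 3.3% and 8.0% re-measured, and 6.8% and 16.3% fixed. From this start, with weight re-measured, 5 L falls short of 7.2% and 8 L exceeds it.

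**Water against tissue, weight re-measured.** Losing 1 L of water lowers the index from 70% to (56 − 1.366)/79 = 69.16%, or 0.84 points. Losing 1 kg of normally hydrated lean tissue gives 55/79 = 69.62%, or 0.38 points. A true loss of 5 kg gives 51/75 = 68%, a relative fall of 2.9%. A 7.2% relative fall needs 4.032/(1 − 0.6496) = 11.5 kg of lean tissue, against 5.6 L of water.

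**Between arms.** On the same assumptions, a mean difference of 1 L in water loss between arms shifts the comparison by about 0.84 points with weight re-measured. With weight fixed the shift is (1/0.732)/80 = 1.71 points.

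**The case against.** The strongest counter-argument is randomisation. The pilot's −7.2% is a change within one arm, and the same sentence reports no fall in the other. Fluid clearance common to both arms cancels on average and leaves noise. A spurious treatment effect needs the arms to differ in fluid, and the article shows no such difference. This stands. A reader might infer that the pilot result was a fluid artefact, or that the planned comparison is biased. The documents support neither: they give no fluid data by arm, and the pilot passage does not even name the device used.

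The match to the pilot figure also depends on assumptions. With weight re-measured and a percentage-point reading, a heavy, lean patient would need nearly 12 L. This stands too: the volumes show what is possible, not what happened.

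A reader might also say that the plan ignores fluid, or errs by giving the fluid estimate no analytic role. It does not ignore fluid, and how the estimate enters the analysis may be set in a full protocol or analysis plan that is not shown. That silence is not counted here.

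Finally, intracellular water is itself derived from a model, and nothing in the article validates it in septic patients. That argues against replacing fat free mass outright. It does not rescue the sentence on proteolysis, which is a stated inference rather than an omitted detail.

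**Conclusion.** The point holds as a limit on interpretation. Percentage fat free mass from bioimpedance cannot by itself show that proteolysis occurred or that muscle was lost or preserved. For the assumed typical patient, a water loss of about 3 to 8 L, depending on how weight is handled and how the pilot figure is read, equals the fall that the article took as muscle loss. With weight re-measured, the index responds about twice as strongly to a litre of water as to a kilogram of lean tissue (0.84 against 0.38 points).

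The conclusion rests on the general bioimpedance principle and on assumed weight, baseline fraction and hydration. It does not establish bias between arms. If the arms did differ in fluid, retention would resemble the hypothesised gain and faster clearance would resemble muscle loss. The added noise could also hide a real effect, but its size cannot be given because the article states no standard deviation. This is a secondary outcome; the primary outcomes are untouched.

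**What to change.** In the Muscle Mass section:

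1. Delete the statement that percentage fat free mass reflects proteolysis, and describe the measure as a hydration-dependent bioimpedance estimate. Reword in the same way the opening statement that it stands for muscle mass.
2. Keep it as the named outcome, so that the Abstract and Hypotheses and Aims remain consistent.
3. Report absolute intracellular and extracellular water from the same spectroscopy readings, by arm, beside the fluid balance already being estimated.
4. State that preserved muscle will be concluded only if the intracellular water result agrees.

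The device, readings and visits do not change. The cost is a little more analysis and a more cautious conclusion, and intracellular water remains a model-based estimate. Comparison with the pilot percentage is kept.

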#### Oxidative Stress Markers

Oxidative stress will be determined through changes in mitochondrial DNA levels. Mitochondrial DNA copy number in the PBMC will be measured by determining relative amounts of mitochondrial to nuclear DNA using quantitative real-time PCR. Mitochondrial DNA (mtDNA) levels in the peripheral blood will be measured at baseline (week 0) and weekly thereafter (till ICU discharge). Total DNA from the blood sample will be extracted from the buffycoat using a DNA Analysis Kit (Machery Nagel Blood XL, Germany) and mtDNA quantity will be analysed using SYBR Green Master Mix Real Time PCR kit (Applied Biosystems, Warrington, United Kingdom). Triplicate analysis of blood samples will be conducted and trends of longitudinal increases in mitochondrial DNA levels will be reported.

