### Oxidative stress

Oxygen-derived free radicals play an important role in the development and progression of disease in critically ill patients resulting in increases in the level of Reactive Oxygen Species (ROS) [26] or decreases in antioxidant defences [27] causing oxidative stress [28]. ROS can play a pivotal role in stimulating the inflammatory system by causing an increase in cytokines (e.g. Interleukins and TNF-α). Both cytokines and ROS can enter the circulation and mediate systemic inflammatory responses linked with clinical conditions [29] which are inter-related in causing muscle proteolysis resulting in the induction of sepsis-induced myopathy [6].

In patients with sepsis, antioxidant depletion has been found to be associated with mitochondrial dysfunction where oxidative stress generates bioenergetic failure [30] which may affect changes in mitochondrial DNA (mtDNA) quantity [31], as well as increase mutations or deletions. This has been hypothesised to be part of the mechanism underlying multiple organ failure and death [32,33].

Oxidative stress also acts as an atrophic stimulus in an unloaded muscle [34] promoting wasting by modifying redox-sensitive processes in its muscle fibres such as during periods of disuse in locomotor skeletal muscles [35] and the unloaded diaphragm during prolonged mechanical ventilation [36,37]. Currently, however, there is no published data on the effects of exercise on oxidative stress on the critically ill population particularly in sepsis.

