### Secondary Outcome Measures

The secondary outcome measures will report on the physiological factors (short-term effects) illustrating underlying mechanisms of early intervention undertaken in the study. Blood samples (8 ml) will be obtained from the patients' arterial line, for the analysis of cytokines, blood lactate and mtDNA levels pre and post intervention during the trial. All blood samples taken will be centrifuged (Spintron GT-25E/LL, Australia) for 15 minutes at 3000 rpm, within 20 minutes of collection. Plasma from the whole blood for the cytokine analysis and peripheral blood mononuclear cells (PBMC) forming the buffy coat pellet for DNA isolation will be stored at -80°C.

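### The mtDNA-to-nuclear DNA ratio in buffy-coat DNA cannot by itself determine oxidative stress, because it can also move with the blood-cell mix; the outcome should be relabelled and its conclusion narrowed

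*Protocol article*

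**What the plan says.** *Oxidative Stress Markers* (Secondary Outcome Measures) states that "Oxidative stress will be determined through changes in mitochondrial DNA levels". The quantity is mtDNA copy number in peripheral blood mononuclear cells, "measured by determining relative amounts of mitochondrial to nuclear DNA using quantitative real-time PCR". The same section says that "Total DNA from the blood sample will be extracted from the buffycoat".

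The opening of *Secondary Outcome Measures* describes one centrifugation, "for 15 minutes at 3000 rpm, within 20 minutes of collection", and refers to "peripheral blood mononuclear cells (PBMC) forming the buffy coat pellet for DNA isolation". The article describes no step that removes granulocytes or platelets.

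On timing, that opening paragraph speaks of blood taken "for the analysis of cytokines, blood lactate and mtDNA levels pre and post intervention during the trial", whereas the specific section says that mtDNA "will be measured at baseline (week 0) and weekly thereafter (till ICU discharge). Total DNA" is then extracted, with no mention of the exercise session.

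On interpretation, the Background section *Oxidative stress* says that oxidative stress leads to bioenergetic failure, "which may affect changes in mitochondrial DNA (mtDNA) quantity". *Hypotheses and Aims* counts an increase in mtDNA as an improvement, and *Oxidative Stress Markers* plans to report longitudinal increases. *Data Management and Statistical Analysis* tests effects of time and of group and names no cell-count covariate. *Sample size* describes mtDNA as one of several pilot measurements in a smaller number of patients.

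**The concern.** There are two gaps between what is measured and what is to be concluded.

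The first is one of construct. A premise that oxidative stress might affect mtDNA quantity, with no direction given, does not support reading oxidative stress off a change in mtDNA. No second marker is listed against which such a reading could be checked.

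The second is one of measurement. In a mixed cell layer the ratio is an average over cell types. Platelets carry mtDNA but no nucleus, so any that remain add to the numerator only. White-cell types may also differ in copies per cell. This is general cell biology; the article neither states nor rebuts it. Table 1 lists an abnormal white-cell count or immature bands among the SIRS criteria, so the cell mix may be disturbed at entry and can shift over weekly samples taken until ICU discharge.

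At stake is what the trial may say. The Background stresses the need to be sure that early exercise in sepsis does not produce oxidative stress, and the Discussion promises findings on oxidative-stress markers. A rise in mtDNA that came only from the cell mix would be in the direction that the protocol treats as benefit.

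**Working it through.** The plan gives no figure for this point that could be reproduced. The check is a mixture identity that shows whether cell mix alone can move the ratio. Every cell count and copy number below is an assumption, because the article gives none.

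**Formula.** With granulocyte count G, mononuclear count M, platelet count P, fraction f of platelets carried into the pellet, and mtDNA copies per cell c_G, c_M and c_P:

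R = (G·c_G + M·c_M + f·P·c_P) / (G + M)

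All copies per cell are held constant, so nothing changes inside any cell. If the material were free of granulocytes and platelets (G = 0, f = 0), then R = c_M and the counts drop out. The concern therefore depends on which cell fraction is actually used.

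**Check 1: white cells only (f = 0).** Set c_G = 1 and c_M = r. Let granulocytes fall from 90% to 70% of white cells.

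- Before: R = 0.9 + 0.1r. After: R = 0.7 + 0.3r.
- r = 2: 1.3 / 1.1 = 1.18 (+18%)
- r = 3: 1.6 / 1.2 = 1.33 (+33%)
- r = 4: 1.9 / 1.3 = 1.46 (+46%)
- r = 1: 1.0 / 1.0 = 1.00 (no change)
- r = 0.5 (granulocytes richer): 0.85 / 0.95 = 0.89 (−11%)

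**Check 2: with platelets.** Assume a septic sample with G = 18, M = 2, P = 150 and a recovered sample with G = 5, M = 3, P = 250 (all ×10⁹/L). The results are recovered R divided by septic R.

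| Assumed copies per cell | Platelets | Recovered / septic |
|---|---|---|
| c_G = c_M = 100 | none carried over | 1.00 |
| c_G = c_M = 100 | 1–4 copies, 10–100% carried over | 1.02 to 1.73 |
| c_G = 100, c_M = 200–300 | 0–4 copies, 10–100% carried over | 1.25 to 2.00 |
| c_G = 200, c_M = 100 | 0–4 copies, 10–100% carried over | 0.86 to 1.31 |

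The extremes, worked:

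- Highest: (18·100 + 2·300 + 150·4)/20 = 150 and (5·100 + 3·300 + 250·4)/8 = 300, so the ratio is 2.00.
- Lowest: (18·200 + 2·100)/20 = 190 and (5·200 + 3·100)/8 = 162.5, so the ratio is 0.86.

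The platelet term f·P·c_P/(G + M) can also fall. Table 1 admits patients with white cells below 4 × 10⁹/L. If their white cells recover while platelets change little, the denominator grows and the ratio drops.

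**Which comparison is exposed.** These figures are changes over time within a patient. If both arms undergo the same shift, say +33%, the between-arm ratio of changes is 1.33/1.33 = 1.00 and the shift cancels. It does not cancel in a within-arm trend or in the time effect.

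**The case against.** **Randomisation.** A reader might infer that recovery from infection would bias the comparison of the arms. The documents do not support that. Recovery happens in both arms and is balanced in expectation, so the 18% to 46% is not a bias in the group contrast. That contrast is affected only if exercise, survival or length of ICU stay changes the cell mix. *Hypotheses and Aims* does expect the intervention to alter inflammation, so this route is possible, but nothing in the article shows it. This objection stands and sets the scope of the point. Balance between arms would still not turn mtDNA content into a measure of oxidative stress.

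**Direction.** It is tempting to say that the ratio will rise with recovery. The assumed values decide this, and some give a fall.

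**Laboratory detail.** A condensed article may leave cell separation to a laboratory manual, and both sections do name mononuclear cells. That is fair: the article does not say that granulocytes or platelets are retained. What remains is that two terms are used for one material.

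**Timing.** A reader might infer that mtDNA is also sampled after exercise. The sentence that suggests this covers cytokines, lactate and mtDNA together, and the specific mtDNA section schedules only baseline and weekly samples. It is a loose end, not a firm contradiction.

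**Safety.** A reader might infer that a safety decision hangs on mtDNA. None does. *Safety and Withdrawal criteria* sets up a separate adverse-event audit, and the Background says only that the physiological measures can help to determine safety.

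**Cell-count adjustment.** Counts taken after randomisation may be mediators, so conditioning on them can bias the group effect. A whole-blood platelet count also does not measure the platelets left in the pellet. Both points stand, and they limit what an adjusted analysis can be used for.

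**Conclusion.** The concern holds in a limited form. The claim that the ratio determines oxidative stress goes beyond the article's own premise, and this part needs no outside assumption. That cell mix alone could move the ratio depends on granulocytes or platelets being present in the extracted layer. On assumed values the movement ranges from a fall of about 14% (0.86) to a doubling (2.00), with +18% to +46% in the white-cell-only example where mononuclear cells are richer in mtDNA. Neither size nor direction can be fixed from the documents.

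The within-arm longitudinal trends and the time effect are the results chiefly exposed. The primary functional and quality-of-life results are untouched. For a secondary, pilot outcome this is a low-priority correction, but it changes what the trial may conclude about oxidative stress.

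**What to change.** 1. In *Oxidative Stress Markers*, name the outcome blood-cell mitochondrial DNA content, in line with the Abstract and *Hypotheses and Aims*, which already speak of mtDNA content. Delete the statement that it determines oxidative stress.
2. State that no conclusion about oxidative stress, or about the safety of exercise in that respect, will be drawn from this outcome alone.
3. Base inference on the unadjusted comparison between arms, and report changes in both directions, not increases only.
4. Add a supportive analysis with neutrophil fraction and platelet count from routine blood counts. Label it interpretive, because these are post-randomisation values that may be mediators, and show it beside the unadjusted result.
5. Make the cell fraction, and the sampling time relative to exercise, consistent between the opening of *Secondary Outcome Measures* and *Oxidative Stress Markers*.

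The cost is small: two routine values abstracted per sample and one extra analysis, with no new samples or assays. The real price is that the trial gives up a direct claim about oxidative stress.
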